**Inclusion criteria:**

AGYW will be eligible for participation in the research study (interviews and/or DBS sampling) if they meet the following criteria:

- Females enrolled or re-enrolled (after a program pause in 2018) on PrEP for 2 to 9 months through the DREAMS initiative
- Consented to be contacted for future studies on the DREAMS program consent form.
- Age 18-24 years
- Residing in select wards of Kisumu or Homabay county
- Provide informed consent to participate in the study

For the IDIs with PrEP continuers, AGYW will be eligible if they meet the following additional criterion:

- Continued with regular PrEP refill visits for at least five months

For the IDIs with PrEP discontinuers, AGYW will be eligible if they meet the following criteria:

- Discontinued PrEP as demonstrated by having missed at least two refill visits (> 60 days overdue) by the time of the 2^nd^ interview and AGYW reports that she is not currently taking PrEP.

AGYW peers will be eligible for participation in the focus group discussions if they meet the following criteria:

- Participating in the DREAMS program but not on PrEP
- Females ages 18+ years
- Residing in select wards of Kisumu or Homabay county
- Provide informed consent to participate in the study

DREAMS Mentors will be eligible for participation in the research study if they meet the following criteria:

- Females ages 18+ years
- Identified by the DREAMS staff as a DREAMS Initiative mentor who coordinates Safe Space activities in the target study wards.
- Provide informed consent to participate in the study

Health care providers will be eligible for participation in the research study if they meet the following criteria:

- Ages 18+ years
- Identified via DREAMS staff as a health provider who provides PrEP services for AGYW in the target study wards
- Received training in PrEP, as per DREAMS program records
- Provide informed consent to participate in the study

AGYW serving as positive controls for DBS collection, storage, and testing procedures must meet the following criteria:

- Female
- Ages 18+ years
- HIV+ Afya Ziwani program participant
- Residing in Kisumu or Nyamira county
- On an ART regimen that includes Tenofovir Disoproxil Fumarate (TDF)
- Virally suppressed, as demonstrated by whole blood plasma testing within the past 4 weeks AND penultimate test also demonstrating viral suppression
- Provide informed consent to participate in the study

**Exclusion Criteria:**

For AGYW, peers, mentor and health care providers, individuals will be excluded from participation in the study based on the following:

- Speaking a language other than English, Dholuo, or Kiswahili
- Unable to provide informed consent due to social or mental challenges

### 6.0 Recruitment

*Recruitment for interviews and DBS*

AGYWs enrolled in the DREAMS Initiative attend safe spaces at least once a month for DREAMS program activities. As part of participating in DREAMS, AGYWs were asked if they were willing to be contacted for future studies and that they would be given the opportunity to decide if they wanted to participate or not.

A random sample of 350 AGYWs from the selected wards who have been enrolled in PrEP for 2 to 9 months, and who indicated willingness to be contacted for future studies, will be generated using a computer-generated random number list, from the DREAMS data for the selected wards. DREAMS participants are identified in the DREAMS data by a unique ID number. The DREAMS team in Kenya (PATH staff who manage the DREAMS project monitoring and evaluation) will link the ID numbers in the drawn sample to the contact information for potential study participants that is recorded/stored separately by the DREAMS project. A study staff will contact the AGYW who have indicated a willingness to be contacted about future studies via phone or at the Safe Space to introduce the study using an approved recruitment script.

The recruitment of participants will take place at monthly PrEP refill visits – designated meeting times when PrEP enrollees come to the Safe Spaces to receive their PrEP refills from providers. DBS sampling will take place at that time, for those who consent to participate. We will make appointments for the interviews to take place after the DREAMS Safe Space meeting, or within the next few days, whichever is convenient for the participant.

*Recruitment for focus group discussions*

For the focus groups with AGYW peers, we will randomly select and recruit 20 AGYW who are participating in DREAMS in the select study wards, but who are not enrolled on PrEP. Focus group participants will be drawn from AGYW attending Safe Space activities, and invited to participate using a standardized recruitment script.

For the focus groups with mentors, we will randomly select potential participants from among those mentors operating in the same wards as the AGYW study participants. Study staff will contact mentors using the contact information available on record and invite them to participate in the study using a standardized recruitment script. Mentors are aware that they may be contacted for research studies and other related activities due to their participation in DREAMS, and as with any participant, may voluntarily choose to participate in the study or not.

Health care providers who are assigned to the DREAMS program Safe Spaces in the same wards as the AGYW study participants, and who have received training in PrEP will be randomly selected and recruited. These providers have responsibility for providing routine PrEP refills and assessments for DREAMS participants at the Safe Space. A study staff will approach health care providers during these visits or at their place of work to ask if they are willing to participate in the study following an approved recruitment script.

*Recruitment for in-depth interviews*

Participants who meet the additional eligibility criteria for either type of IDI (continuing PrEP or discontinuing PrEP) will be randomly selected from among those participating in the second interviews. In-depth interviews will be audio-recorded, conducted at a place of convenience to the respondent, and lasting no more than one hour.

*Recruitment of positive controls*

The Afya Ziwani team collects data on HIV+ AGYW who participate in their program. Based on their program records, the Afya Ziwani team will identify a convenience sample of potential positive controls who meet the eligibility criteria (female 18+ years old, living in Kisumu or Nyamira county, taking tenofovir for ART, virally suppressed as per testing within the past month, and penultimate viral load test demonstrating suppression). An Afya Ziwani staff person will contact the individual about their willingness to be contacted about future studies via phone or at the Safe Space. S/he will introduce the study and their specific role in the study using an approved recruitment script. The role of the Afya Ziwani project staff (who are not research staff) ends with identification and preliminary recruitment of potential participants whose medical records suggest they fit the eligibility criteria. Once a potential participant agrees to meet with a PATH research staff person, all study procedures are conducted by study staff, including informed consent, verification of eligibility and DBS sampling.

For those who are interested, an appointment will be made to assess eligibility and conduct the informed consent. Note that the consent form includes release of the patient information relevant for eligibility assessment (type of ART, viral load at most recent test, date of most recent test, viral load at penultimate test); study staff will be blinded to this patient information unless the participant consents to share it. For individuals who are eligible and consent to participate, a DBS will be collected. Once the DBS is collected, their participation in the study ends.

Recruitment and participant engagement procedures will be adapted to the COVID context. Specifically, the procedures outlined below will be followed to ensure the safety of participants and research staff:

- We will comply with country and county public health authorities and government requirements. Through Afya Ziwani, the study team will meet with members of sub-County and County Health Management to discuss study plans including plans to adhere to all COVID-19 protocols.
- We will ensure that water and soap for handwashing and/or hand sanitizers are available in all locations where individuals will meet the study team. In addition, we will provide participants in this study with a face mask.
- DBS samples will be collected at a central place. The study team will cater for transport costs for both the participant and the study team. Transport costs incurred by participants to come to central locations for purposes of the study will be reimbursed as per PATH Kenya guidelines. We will ensure that individuals follow the recommended guidelines for physical distancing when using public means to travel to these locations.
- Data collection will be done through finger prick for purposes of DBS collection. We will ensure that the study team member performing the DBS procedures and the participant wear a face mask throughout the contact period.
- Further, we will ensure the study team member and the participant maintain physical distance of at least 2 meters except while pricking the participant’s finger and drawing her blood.
- DBS collection will be done in an open and secluded space, away from buildings and with one participant at a time.
- The study team will carry an infrared thermometer for checking their own and study participants’ temperature.
- Participants and the study team will be informed not to come for any in-person data collection activity if they are not feeling well.

### 7.0 Illustrative lines of inquiry

**AGYW participant**:

| **Topic** | **1^st^ interview** | **2^nd^ interview** |
| --- | --- | --- |
| Principal rationale or motivation for participating in the DREAMS program | X |  |
| Principal rationale or motivation for initiating PrEP | X |  |
| Experience of care, receiving PrEP via Safe Spaces | X |  |
| Self-reported adherence to PrEP regimen | X | X |
| Perceived challenges with PrEP adherence | X | X |
| Reasons for discontinuing PrEP |  | X |
| Level of social support (including partner, family and community) for PrEP | X | X |
| Current level of HIV risk and perception of HIV risk | X | X |
| Perceived HIV stigma | X | X |
| Perceived efficacy of PrEP | X | X |
| Degree of self-efficacy/personal empowerment | X |  |
| Indicators for depression/mental health | X | X |
| Alcohol use | X | X |
| Experience of violence | X | X |
| Food security | X | X |

**AGYW focus groups**:

- Level of engagement and support in/for DREAMS Initiative
- Beliefs about factors that increase or decrease risk of HIV acquisition
- Stigma associated with HIV
- Perceptions, attitudes and beliefs about PrEP use and AGYW who take PrEP

**DREAMS mentor focus groups**:

- Awareness of factors that impact AGYWs’ enrollment on PrEP, including social and cultural factors that facilitate or impede PrEP use
- Awareness of factors that impact PrEP adherence.
- Perceptions about benefits and challenges of providing PrEP at community venues compared to health facilities

**Health care provider** focus groups:

- Attitudes, beliefs regarding provision of reproductive health services to AGYW
- Perception of level of community support for DREAMS, PrEP
- Perceptions about benefits and challenges of providing PrEP at community venues compared to health facilities
- Knowledge of social and cultural factors that facilitate or impede PrEP use.

**AGYW PrEP continuing participant:**

- Assessment of satisfaction with DREAMS program activities
- Deeper exploration of principal rationale or motivation for initiating PrEP
- Deeper exploration of level of social/community support for PrEP
- Deeper exploration of perceived challenges with PrEP adherence

**AGYW PrEP discontinuing participant**:

- Assessment of satisfaction with DREAMS program activities
- Exploration of rationales for discontinuing PrEP
- Deeper exploration of perceived challenges with PrEP adherence
- Perceived level of social/community support during PrEP use
- Deeper exploration of current level of HIV risk and perception of HIV risk

### 8.0 Consent process

The consent process for AGYW will take place in a private setting at the DREAMS program safe spaces for AGYW. If preferred by participants, the consent process may also be conducted at other community locations, places of residence or place of work.

Study staff will explain all aspects of the study to the potential participants, emphasize that participation in this study is voluntary, and that the health care services that a participant receives will not be affected by her decision to participate or not in the study. Potential participants will be given the opportunity to read the consent themselves and to ask questions of the study staff.

If a potential participant is unable to read the consent and requires it to be read to her, a literate, impartial witness will serve as a consent witness to ensure that the participant understands the study information, including risks and benefits. In addition to being literate, the witness must not be a member of the research team or a PATH staff person. A Safe Space mentor or health care provider are examples of suitable informed consent witnesses. Note that the witness would exit the room following the consent process and therefore would not be present during the interview.

Once all the potential participant’s questions have been answered satisfactorily, potential participants will be given the opportunity to voluntarily indicate if they wish to participate in the study. If an individual agrees to participate, she will be asked to sign, or give her initials if she is unable to sign. Participants will sign two identical consents and will be given a copy of one of the consents to take home.

The consent process for positive controls is the same as for AGYW study participants, though the consent form itself is tailored to their role.

The consent process for the focus group discussions may be conducted individually or in a group setting, given the low risk of the activity. Basic demographic information (age, education, marital status, length of involvement in DREAMS, job title (providers)) will be collected from participants for the purposes of defining the focus group population. Personal identifiers will not be collected. Given the anonymity of their participation in the FGD process and low risk of the activity, consenting for focus group discussions will be oral, with the study staff signing to verify that the consent process was followed. A consent log will be created to track the consent status of each individual recruited.

For the in-depth interviews and focus group discussions, participants who are unwilling to be audio-recorded will not participate.

Study staff responsible for obtaining consent will be trained in human subjects protection, including the importance of not coercing or influencing individuals’ decision to participate in the study. A private setting will be used for the consent process in order to protect the privacy and confidentiality of potential participants during the process.

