**Figure 2: Sample of AGYW study participants**

**Sample at Time 1** **Sample at Time 2**

Longitudinal sample

Longitudinal sample

We will supplement and enhance our understanding of factors critical to PrEP adherence through qualitative data collection. Specifically, we will conduct two focus groups with AGYWs who are 18+ years old (AGYW peers) but not enrolled on PrEP, two focus groups with DREAMS health care providers and two focus groups with DREAMS mentors who coordinate the DREAMS Safe Space activities. The AGYW peer focus groups are intended to explore the influence of peers on AGYWs’ PrEP enrolment and adherence. We target AGYW who are not themselves enrolled on PrEP in order to better understand the social climate in the communities where our participants reside. Understanding the social environment is critical for studies involving AGYW because of the strong influence these social spheres have over AGYW’s health and behavior.^[[46]](#endnote-46)^ Focus group participants will be drawn from the same wards as the AGYW who participate in interviews and biomarker sampling.

Finally, we will conduct in-depth interviews (IDIs) with a subsample of 16 AGYW 18+ years who are continuing with PrEP and in-depth interviews with 16 AGYWs 18+ years who have discontinued PrEP entirely. These interviews are for the purposes of illuminating in a qualitative fashion some of the underlying behavior rationales affecting adherence as well as the underlying reasons *why* AGYWs discontinue PrEP use after enrollment. The samples of AGYW for the IDIs will be randomly drawn from among those participating in the quantitative survey (a subsample of respondents).

The outcome measure or study endpoint will be PrEP adherence as measured by the biomarker level of tenofovir. Multivariate regression analysis will determine whether differences in adherence are associated with any particular contextual co-factors. Specifically, we hypothesize that the following measures will be positively associated with PrEP adherence:

- AGYW perceived HIV risk and perceived efficacy of PrEP
- Internal and perceived HIV stigma
- Level of personal empowerment
- Perceived social support of family, friends (MODS survey)
- Trust, confidence in provider and mentor
- Level and nature of involvement in DREAMS activities
- Regularity of PrEP provision at Safe Spaces
- Receptivity of provider to AGYW use of PrEP
- Community support for DREAMS, PrEP
- Lower depression scores (PHQ-9)

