In addition to the DBS collected from study participants, we will recruit, consent, and collect a DBS from up to 10 HIV+ AGYW who are on ART (TDF) and virally-suppressed to serve as positive controls for the purpose of validating the DBS storage and testing procedures. Because these individuals are virally suppressed from their ART, their DBS test results will show adherent tenofovir levels, assuming an accurate test assay and effective DBS collection, storage, and transfer procedures. Other than the DBS, their age, their length of time on ARTs, and duration of viral suppression (if known), no additional information from these positive controls will be collected. To clarify, these participants are not contributing toward the achievement of the study objectives per se, nor providing data for the analysis, but are critical to validate that the DBS testing results obtained from study participants are accurate measures of PrEP adherence. PATH has a project, called Afya Ziwani, that provides services to HIV+ individuals in Kisumu and Nyamira counties and therefore is able to identify women on ART who, if willing, could serve as positive controls.

*Quantification of PrEP Adherence:* We will measure tenofovir diphosphate (TFV-DP) in finger-prick whole blood dried blood spots. Dried blood spots (DBS) have been demonstrated to be a suitable measure for TFV-DP, as a long-term measure of TDF and PrEP adherence. Approximately 2.5 ml of blood is required for the dried blood spot card.

All drug measurements will be performed at the Program for HIV Prevention and Treatment (PHPT) laboratory at Chiang Mai University (ISO:15189 certified), pharmacology laboratory established by [name] in 2003. The Chiang Mai University laboratory is approved by the Division of AIDS (DAIDS) to perform antiretroviral drug level measurements by liquid chromatography dual mass spectrometry (LC-MS/MS), and is the reference laboratory for IMPAACT and DAIDS studies in Thailand. In accordance with DAIDS polices, the lab participates in the Clinical Pharmacology Quality Assurance and Quality Control Program (CPQA).[^63^](#_ENREF_63) The CPQA program includes regular proficiency testing, external review of SOPs/validation reports, and audits. Drug assays used by the lab are validated based on the US FDA ‘Bioanalytical Method Validation’ guidelines.

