### 9.0 Risks

The risks for participants in this study due to the study procedures (interview) are anticipated to be minimal. Because our target population is AGYW who are enrolled in the DREAMS program, they are more accustomed than the average Kenyan woman to discussing sensitive topics. As an example, AGYW who are taking PrEP are asked on a quarterly basis about their risk factors for HIV infection, including questions that concern transactional sex, the number of sexual partners, gender-based violence, etc. The risks associated with participating in the current study may include the following:

Psychological risk: Participants may feel embarrassment or discomfort discussing sensitive topics such as sexual behavior, HIV services used, etc.

Social risk: There is a risk of a breach of confidentiality, which could put an individual at risk if someone were to find out sensitive and confidential information about the AGYW. For the positive controls, a breach of confidentiality could reveal her status as HIV+. Similarly, if there were a breach of confidentiality, a health care provider could be put at risk with her/her employer or community if his/her responses were viewed negatively.

In the focus group discussions, the study will ask participants not to talk with others outside the study about who was in the group or what was discussed. However, there is the risk that a participant may breach this. Also note that, by participating in an FGD, the individual is self-disclosing to other participants that they are involved in the DREAMS program, either as a participant (peer), provider, or Safe Space mentor.

Physical risks (blood sample): The participant will likely feel some pain when the staff conducts the fingerstick to take the blood sample. Other than this brief pain, the discomfort of the finger prick is minimal. This pain is comparable for tests for HIV infection, which are conducted on a quarterly basis with all PrEP participants. In about one out of 10 cases, people have a small amount of bleeding under the skin or a bruise. For some people they may have a small scar for a few weeks. The risk for localized infection from the fingerstick is less than 1 in 1,000.

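### Section 8.0 applies the PrEP users' consent-witness rule unchanged to HIV-positive controls, so a Safe Space mentor could learn a non-reading control's status before she has consented

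*Protocol*

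**What the plan says.** Section 8.0 (Consent process) calls for a witness in one situation: "If a potential participant is unable to read the consent and requires it to be read to her". The witness must be literate and impartial and is there to make sure that she understands the study information. One group is barred: "the witness must not be a member of the research team or a PATH staff person". Two kinds of person are then offered: "A Safe Space mentor or health care provider are examples of suitable informed consent witnesses".

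The section closes its account of the PrEP users' consent by extending it: "The consent process for positive controls is the same as for AGYW study participants, though the consent form itself is tailored to their role".

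The controls are described in Section 4.0, which plans to "collect a DBS from up to 10 HIV+ AGYW who are on ART (TDF) and virally-suppressed". They come through a separate programme: "PATH has a project, called Afya Ziwani, that provides services to HIV+ individuals". Section 6.0 (Recruitment of positive controls) says that their consent form includes release of the type of antiretroviral therapy and the last two viral load results.

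Section 9.0 (Risks) names the harm at issue: "For the positive controls, a breach of confidentiality could reveal her status as HIV" (the plus sign follows in the text). Section 10.0 (Mitigation of risks) answers it with a private setting and, for controls, the option not to take a copy of the form. It also has consent witnesses trained in research ethics, with stress on confidentiality and privacy.

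**The concern.** The witness rule was written for PrEP users at DREAMS Safe Spaces. For them, a mentor or provider from that setting is a natural choice. The controls are different: they are patients of another programme, and what marks them out is that they are HIV-positive. A form tailored to that role cannot be read aloud without revealing it.

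For a control who cannot read, the disclosure would not need a lapse by anyone. A witness who did not already know her status would learn it by doing the job that Section 8.0 assigns, before she has decided whether to join. This is the harm that Section 9.0 singles out for controls. Under Section 11.0 participants get no direct benefit, and under Section 4.0 the controls serve only to validate the blood-spot procedures.

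**Working it through.** No arithmetic decides this point, so the check sets the relevant sections side by side.

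1. **When is a witness present?** Only when the woman cannot read the form and needs it read to her (Section 8.0).
2. **Who may witness?** The binding conditions are literate, impartial, and neither research team nor PATH staff. Mentor and provider are examples. Nothing excludes a Safe Space mentor (Section 8.0).
3. **Does this hold for controls?** Yes. Section 8.0 says their process is the same and changes only the form. Sections 8.0 to 10.0 contain no separate witness rule for controls.
4. **What would the witness hear?** A form that covers release of antiretroviral regimen and viral load results (Section 6.0). Her HIV status follows from that content.
5. **When?** During the reading, so before consent. Section 6.0 keeps study staff blinded to the control's eligibility information unless she consents to share it. The witness is under no matching restriction on learning her status.
6. **Is a mentor a realistic witness for a control?** It is possible. Section 5.0 has controls living in Kisumu or Nyamira. Section 1.0 places the DREAMS work that PATH leads in Kisumu and Homabay, so the overlap is Kisumu. Section 6.0 allows first contact with controls by phone or at the Safe Space.
7. **Do the safeguards reach it?**
   - Private setting (Section 10.0): the witness is inside it.
   - Declining the copy (Section 10.0): this deals with the paper, not with the person who heard it read.
   - Witness training (Section 10.0): this limits what the witness passes on, not what she or he learns.
   - Witness leaving before the interview (Section 8.0): this gives a control nothing, since she gives a blood spot and has no interview.

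**Size.** Let k be the number of controls who cannot read and whose witness does not already know their status. With at most 10 controls, 0 ≤ k ≤ 10. The protocol gives no literacy figure and does not say who would be chosen as witness, so k cannot be narrowed further.

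**The case against.** The strongest reply is that the rule permits this outcome but does not require it. Mentor and provider are only examples. A provider who already treats the woman for HIV, and is not PATH staff, is allowed under the present text, and a sensible team would probably choose such a person. Few women could be affected. The protocol plainly recognises the disclosure risk, trains the witnesses, and adapts the copy rule for controls. The tailored form is not among the pages available, so it may itself deal with the witness. All of this stands and keeps the point small. It does not close the gap, because Section 8.0 sets the procedure, names a mentor as suitable and calls the controls' process the same.

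A reader might infer more than the protocol supports:

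- **That the procedure discloses status as a matter of course.** It does not. A witness is used only for non-readers and may already know the status.
- **That witness confidentiality is ignored.** Section 10.0 provides training on exactly that.
- **That barring PATH staff shuts out everyone who knows her status and so forces the use of a mentor.** Afya Ziwani is a PATH project, but the protocol does not say that all who care for these women are PATH staff. The bar also protects independence, since PATH runs the study.
- **That mentors and providers are equally unsuitable for PrEP users**, because Section 3.0 lists "Trust, confidence in provider and mentor" among the factors studied and both groups supply focus-group participants. This is debatable. Providers at the Safe Space already know of the PrEP use, and an outsider could newly learn of it. The witness leaves before the interview, and only a random selection of mentors and providers joins the focus groups.
- **That a definite number of women would be exposed.** Any such figure would rest on a literacy rate that the protocol does not give.

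**Conclusion.** The point holds as a narrow gap in participant protection. Section 8.0 carries the PrEP users' witness rule over to the HIV-positive controls without adapting it. As written, it permits a Safe Space mentor who does not know a control's status to learn it before she consents. The authors saw that the PrEP users' process did not fully suit controls, since they changed the rule on the take-home copy, but they left the witness rule as it was.

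The size is between zero and a few women, at most 10, and cannot be stated more closely. The conclusion rests on two assumptions: that at least one control may be unable to read, and that the form read aloud contains what Section 6.0 says it contains. No endpoint, power figure or analysis depends on it. It merits a change because the possible harm to the woman concerned is serious and the change costs almost nothing.

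**What to change.** Add a short paragraph to Section 8.0, and match it in the consent procedures, stating for positive controls that:

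- the witness is not a Safe Space mentor;
- the witness is literate, impartial and outside both the research team and PATH staff, as now;
- the witness either already knows her HIV status (for example a non-PATH provider already giving her HIV care), or is someone she accepts after being told privately, before the form is read, that the witness will learn her status.

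The rule for PrEP users can stay as it is, and so can the witness training in Section 10.0.

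The cost is one paragraph. A suitable witness may be harder to find for a few controls, and some may not be enrolled. That is tolerable because the control sample has only an upper limit of 10 and does not contribute to the study analyses.
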